### Statistical analysis

The data collected will be stored in locked cabinets, and only the blinded assessor will have access to this information. Data will be saved in a computer spreadsheet with password protection to ensure confidentiality. To ensure no error, the spreadsheet will be monthly monitored and audited by a researcher who is blind to the participants’ group allocation and has no conflict of interest. The mean effects of the interventions and the differences between groups for all outcomes and their respective 95% confidence intervals will be calculated using linear mixed models, which will incorporate terms for the treatment groups, time (i.e. three variables will be created for the categories baseline, 8-week and 6-month follow-ups), and interaction terms (treatment groups versus time). Treatment coefficients versus time interactions will be equivalent to the estimates of the differences between groups. The analyses will follow the principles of intention to treat and no interim analyses will be performed. No additional analysis will be performed. If a patient drops out of treatment, no additional outcome will be collected. The significance level will be set at 5%, and SPSS for Windows will be used for the statistical analysis.

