### Sample size

The study was designed to detect a clinically significant 2-point difference in pain intensity assessed by the Pain Numerical Rating Scale (estimate for standard deviation = 2.5) and a 5-point difference in disability assessed by the Roland Morris Disability Questionnaire (estimate for standard deviation = 6.5) [49, 50] eight weeks after randomization, using a two-tailed t-test of difference between means and assuming α = 0.05, statistical power of 80% [51], and loss to follow-up of 15%. Estimations indicated that 34 patients per group will be required using pain intensity to calculate sample size, and 37 patients per group using disability. Therefore, the biggest number resulting from sample size calculation will be considered, which corresponds to 74 patients. To reach this number, the study will be promoted in community newspapers and on the internet.

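### The primary estimate is an unadjusted difference in change from baseline; using the baseline score to adjust would be at least as precise, usually more so, at no cost

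*Protocol article*

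**What the plan says.** The Statistical analysis section of the protocol article specifies a linear mixed model for every outcome, "which will incorporate terms for the treatment groups, time (i.e. three variables will be created for the categories baseline, 8-week and 6-month follow-ups", plus interaction terms. It identifies the treatment effect with the interaction: "Treatment coefficients versus time interactions will be equivalent to the estimates of the differences between groups". It then adds: "No additional analysis will be performed". Baseline is thus one level of the outcome, the group term is unconstrained, and neither a baseline covariate nor a common baseline mean is mentioned.

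The Sample size section bases the number of patients on the 8-week comparison, "using a two-tailed t-test of difference between means and assuming α = 0.05". It uses 2 points with SD 2.5 for pain and 5 points with SD 6.5 for disability, 80% power and 15% loss. It gives no correlation between baseline and 8 weeks, and does not say whether the SDs describe scores or changes.

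**The concern.** With a free group term and baseline as reference, the group × 8-week coefficient is the difference between groups in mean change. This subtracts the whole of the observed baseline imbalance, whatever the correlation. Patients are randomised after the baseline assessment, so the true baseline means are equal in expectation and that imbalance is chance. Adjustment removes only the part of it that predicts the 8-week score, and so adds less noise.

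What is at stake is precision. The trial has 74 patients, and baseline pain and disability are already measured on all of them. They could narrow the confidence interval for both primary outcomes without another patient or visit. The text fixes the estimate and rules out further analyses, so this is a stated choice and not a detail left open.

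**Working it through.** **Inputs.** From Sample size: pain difference 2, SD 2.5 (standardised 2/2.5 = 0.800); disability difference 5, SD 6.5 (5/6.5 = 0.769); two-sided alpha 0.05; loss 15%; 37 per group. Evaluable per arm: 37 × 0.85 = 31.45, taken as 31. Assumed, because the article gives no values: rho, and k = baseline SD / 8-week SD.

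**The plan's own figures.** For 80% power, n per arm = 2(1.96 + 0.84)² / (standardised difference)².
- Pain: 25 (26 with the t distribution), or 30 to 31 after dividing by 0.85. The plan states 34.
- Disability: 27 (28), or 32 to 33 after loss. The plan states 37.

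The stated numbers do not reproduce at 80% power; they fit about 85%. With 31 per arm, a t-test of 8-week means has power 87% (pain) and 85% (disability). This slack matters below.

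**Variance per patient**, with s the 8-week SD:
- difference in change: s²(1 + k² − 2·rho·k)
- baseline-adjusted: s²(1 − rho²)
- 8-week score alone: s²

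The first minus the second is s²(k − rho)², so

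ratio = 1 + (k − rho)² / (1 − rho²).

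This is never below 1. With k = 1 it reduces to 2/(1 + rho).

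| rho | k = 1 | k = 0.8 | k = 0.7 |
|---|---|---|---|
| 0.3 | 1.54 | 1.27 | 1.18 |
| 0.5 | 1.33 | 1.12 | 1.05 |
| 0.7 | 1.18 | 1.02 | 1.00 |

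For example, at k = 0.8 and rho = 0.3: 1 + 0.5²/0.91 = 1.27. The change estimate is less precise even than the 8-week means alone when rho < k/2, that is below 0.50, 0.40 and 0.35 for the three columns.

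**Power if 2.5 and 6.5 are score SDs and k = 1** (noncentral t, 31 per arm; pain / disability). The standardised difference is divided by √(2(1 − rho)) for change and by √(1 − rho²) for adjusted.

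| rho | change | adjusted |
|---|---|---|
| 0.3 | 75% / 71% | 90% / 88% |
| 0.4 | 81% / 78% | 92% / 90% |
| 0.5 | 87% / 85% | 95% / 93% |

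Change-score power drops below 80% at rho under 0.39 (pain) or 0.43 (disability).

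**If the mixed model also uses the baselines of patients later lost** (37 baselines and 31 week-8 values per arm, k = 1), the variance per arm of the change estimate, in units of s², is (1 − rho²)/31 + (1 − rho)²/37. By normal approximation, power at rho 0.3 is 78% / 75% and at 0.4 it is 84% / 81%. The 80% thresholds become 0.33 (pain) and 0.385 (disability). The variance ratio against the constrained model is then 1.45 at rho 0.3, 1.28 at 0.5 and 1.15 at 0.7.

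**If the baseline SD is smaller** (31 completers, rho 0.3), change-score power is 82% / 79% at k = 0.8 and 85% / 82% at k = 0.7.

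**If 2.5 and 6.5 are SDs of change**, the sample-size test is the planned test, and power is 87% / 85% at any rho.

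**The case against.** The strongest reply is that nothing here is invalid. The difference in change is unbiased under randomisation and keeps its nominal type I error, and sizing a trial with a t-test while analysing it with a mixed model is common practice. That stands, and it limits the point to efficiency.

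Three stronger readings are tempting, and the document supports none of them.

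- *The trial is underpowered.* That needs score SDs, near-equal variances and a rho below roughly 0.33 to 0.43. The article settles none of these. The entry rule of pain at or above 3 makes a modest rho plausible for pain, but it also tends to shrink the baseline SD, which reduces the shortfall or removes it. There is no entry threshold on the Roland Morris score, the outcome that set the sample size.
- *The ratio 2/(1 + rho) applies whatever SD was meant.* It holds only when the baseline and 8-week variances are equal; the general formula gives smaller values for k = 0.8 and 0.7.
- *Three time variables make the model rank-deficient, or turn the 8-week coefficient into a contrast with 6 months.* The words "three variables will be created for the categories baseline, 8-week and 6-month follow-ups" describe a three-level factor, and software handles the redundancy routinely. Equating the interactions with the between-group differences already implies baseline as the reference.

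What the reply does not touch is that the adjusted estimate has the smaller variance unless k equals rho, and then the two are equal. It uses data already collected.

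**Conclusion.** The point holds as a free improvement in precision. The planned 8-week estimate is an unadjusted difference in change, and its variance exceeds that of a baseline-adjusted estimate by the factor 1 + (k − rho)²/(1 − rho²). With equal SDs and rho between 0.3 and 0.5, adjusting is worth as much as 33% to 54% more patients. With a baseline SD at 0.8 of the 8-week SD, the gain over the same range is about 12% to 27%. These figures take completers only and rest on assumed values of rho and k.

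A loss of power below the stated 80% is possible but conditional, and it disappears if the quoted SDs are SDs of change. There is no bias and no error in the test.

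**What to change.** Keep the mixed model and constrain the two groups to a common baseline mean: baseline as the reference time, two time indicators, group × 8-week and group × 6-month terms, and no group main effect. Alternatively, model the 8-week and 6-month scores with the baseline score as a covariate. In either case, name the 8-week group contrast as the primary estimate for pain and for disability. It would also help to say in Sample size whether 2.5 and 6.5 are SDs of scores or of change.

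The cost is one sentence of analysis text and a clause in the sample-size text. It needs no new data and no extra patients, and it runs in the software already named. It should be settled before the data are analysed.

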### Assessment

Before assessment, written consent will be obtained from the patients. A blinded assessor, who is a physical therapist with five years of clinical experience, will evaluate the eligible participants in person. The evaluation will consist of: personal data, clinical data, and evaluation of outcomes. The initial assessment will be conducted prior to the random distribution of the patients into the treatment groups, in a reserved place. The assessment of the outcomes will be repeated eight weeks and six months after randomization in the same place. To prevent loss of follow-up, patients will be asked to be available nearly the dates of follow-ups.

The primary outcomes will be pain intensity and disability, assessed eight weeks after randomization. Secondary outcomes will be as follows: global perceived improvement, specific disability, dynamic balance, muscle strength (gluteus maximus, gluteus medius, and hip lateral rotators), and pressure pain threshold, assessed eight weeks and six months after randomization. Pain intensity and disability assessed six months after randomization will be considered as secondary outcomes too. All the questionnaires/scales used in this study show adequate measurement properties [22, 26, 27].

The pain intensity perceived by the patient in the last seven days will be evaluated by the 11-point Pain Numerical Rating Scale [22], with zero being “no pain” and 10 being “pain as bad as could be”. This scale will also be applied daily before each treatment session in relation to pain intensity in the last 24 h. The pain assessment will be conducted verbally.

Disability associated with low back pain in the last 24 h will be assessed using the Roland Morris Disability Questionnaire [22, 26, 27], consisting of 24 items that describe daily activities that patients often report difficulty performing due to low back pain. The answers are yes/no, and each affirmative answer is worth one point. The final score is calculated by adding all the points. The higher the score is, the greater the limitation.

The global perceived improvement comparing the onset of symptoms to the last few days will be assessed using the Global Perceived Effect Scale [22]. It is an 11-point numerical scale (− 5 to 5), with − 5 being “vastly worse”, 0 “no change”, and 5 “completely recovered”.

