### Randomization and interventions

Randomization will be performed by a researcher not involved in the recruitment, assessment, or treatment of the participants by means of a random numerical sequence generated by Microsoft Excel 2010, before the beginning of the study. Treatment allocation will be concealed through sealed, opaque envelopes sequentially numbered. After the baseline assessment, one of the therapists responsible for the intervention will open the sealed envelope to identify the group to which the participant was allocated (Pilates Group or Aerobic Group). This is a single-blind study because only the assessor will be blind to the allocation of the participants in the treatment groups. Due to the nature of the interventions, it will not be possible to blind participants and therapists. At the end of the study, the assessor will say to which group he believes the participants were allocated in order to test the blinding of the study.

Both groups will receive 16 individual, twice-weekly exercise sessions lasting 60 min each over a period of 8 weeks. To improve adherence, participants will receive a calendar with the sessions date and the available days for missed sessions. This will ensure that the intervention period and the make-up sessions do not exceed 10 weeks, when the treatment will end, independently of the number of sessions achieved. Additionally, in São Paulo, older adults aged above 60 years do not pay for public transportation, which could ensure participants to come to the intervention site. Sessions will be supervised by two physical therapists. The Pilates Group will be supervised by a physical therapist certified in Pilates with four years of experience with the method, and the Aerobic Group will be supervised by a physical therapist specialized in Sports Physical Therapy with one year and six months of experience and specifically trained with the proposed exercises. Patient chart will be audited monthly for protocol deviations by an independent researcher. The treatments are described in Table 1. Patients will be asked to not look for other treatments outside the trial during the intervention period. Adverse events will be collected during the intervention period. Table 2 shows the timeline of the study.

**Table 1 Tab1:** Description of the interventions

Group	Description

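### Outcome collection stops at treatment drop-out, so the intention-to-treat comparison rests on patients who stayed plus an untestable missing-at-random assumption

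*Protocol article*

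**What the plan says.** Three statements stand close together in the protocol article, Statistical analysis:

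- On the analysis set: "The analyses will follow the principles of intention to treat and no interim analyses will be performed".
- On further analyses: "No additional analysis will be performed".
- On patients who leave treatment: "If a patient drops out of treatment, no additional outcome will be collected".

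The effects "will be calculated using linear mixed models, which will incorporate terms for the treatment groups, time" and their interaction, with baseline, eight weeks and six months as the time categories.

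Two other sections fix the timing. Under Assessment: "The primary outcomes will be pain intensity and disability, assessed eight weeks after randomization". Under Randomization and interventions: "Both groups will receive 16 individual, twice-weekly exercise sessions lasting 60 min each over a period of 8 weeks". Make-up sessions are allowed, provided that the intervention period and these sessions "do not exceed 10 weeks, when the treatment will end, independently of the number of sessions achieved".

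The Assessment section asks patients to be available near the follow-up dates. Nothing in the article provides for follow-up of someone who has stopped treatment.

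**The concern.** Intention to treat needs outcomes from all randomised patients, whether or not they keep to treatment. A rule that ends measurement when treatment ends early works against this. Programme and primary time point coincide, so drop-out from treatment will usually mean that the primary outcome is missing.

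Stopping an exercise programme may well be linked to pain, lack of benefit or intolerance, so missing at random given arm and baseline is least credible for these patients. The two programmes could also lose patients at different rates or for different reasons. Pilates exercises are chosen by preference and adapted if pain worsens, the comparator is treadmill walking, and patients and therapists are unblinded. If so, the primary contrast is shifted in favour of the arm that loses more patients with poor outcomes. The Discussion calls the study pragmatic and at low risk of bias, and both claims depend on the effect in everyone randomised.

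A later analysis plan can change the model, but it cannot recover outcomes that were never collected.

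**Working it through.** **Inputs from the protocol article**

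- Sample size: "2-point difference in pain intensity assessed by the Pain Numerical Rating Scale (estimate for standard deviation = 2.5"; loss to follow-up 15%; 37 per group, 74 in total. Fifteen per cent of 74 is 11.1, so about 11 patients.
- Statistical analysis: the model uses baseline, eight weeks and six months only.
- Not given: drop-out by arm and the outcomes of drop-outs. The values used for these below are assumptions.

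**The plan's own figure.** A two-sided t-test at 80% power needs 26 per group for pain, and 26 / 0.85 = 30.6, so 31 (34 stated). For disability it needs 28, and 28 / 0.85 = 32.9, so 33 (37 stated). The stated numbers fit about 85% power. They err on the large side and do not bear on this point. With about 31 per group observed (37 × 0.85 = 31.45), power is 87.3% for pain and 84.6% for disability. The harm is therefore bias, not lost power.

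**What the planned model estimates.** In each arm let p be the drop-out rate and g the amount by which drop-outs would score worse at eight weeks than stayers with the same baseline.

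- Mean in everyone randomised = stayers' mean + p × g.
- An early drop-out has neither an eight-week nor a six-month value, so the model fills the gap from arm and baseline alone. It returns the stayers' mean, adjusted for baseline.
- Bias of the contrast A − B = pB × gB − pA × gA, which is (pB − pA) × g if the gap is the same in both arms.

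| Assumed drop-out, B v A | Assumed gap (points) | Bias (points) | Share of 2-point target |
|---|---|---|---|
| 20% v 10% | 1 | 0.10 × 1 = 0.1 | 5% |
| 20% v 10% | 2 | 0.10 × 2 = 0.2 | 10% |
| 20% v 10% | 3 | 0.10 × 3 = 0.3 | 15% |
| 25% v 5% | 1 | 0.20 × 1 = 0.2 | 10% |
| 25% v 5% | 2 | 0.20 × 2 = 0.4 | 20% |
| 25% v 5% | 3 | 0.20 × 3 = 0.6 | 30% |
| 15% v 15% | any, equal in both arms | 0 | 0% |

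The unequal pairs average 15%, the article's own overall figure.

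**Simulation check.** Settings: 37 per group, SD 2.5, an assumed baseline to eight-week correlation of 0.5, no difference between arms among stayers, and 4,000 repetitions of the two-time-point likelihood estimate.

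| Drop-out A v B, gap | Model estimate | All randomised | Bias |
|---|---|---|---|
| 10% v 20%, 2 | −0.007 | −0.203 | 0.196 |
| 5% v 25%, 2 | 0.005 | −0.393 | 0.398 |
| 5% v 25%, 1 | −0.004 | −0.203 | 0.198 |
| 5% v 25%, 0 | 0.015 | 0.017 | −0.002 |
| 15% v 15%, 2 | 0.011 | 0.009 | 0.003 |

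The simulation agrees with the formula. The 3-point rows rest on the formula alone.

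**Within-arm means.** With equal 15% drop-out the contrast is unbiased, but each arm's mean improvement is overstated by 0.15 × 1 = 0.15 to 0.15 × 3 = 0.45 points.

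**The case against.** Much of the case on the other side stands, and it limits the point.

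- *An intention-to-treat analysis is impossible.* A reader might infer this, but the article does not support it. Baseline is one of the model's time categories, so every randomised patient enters as allocated. What is lost is the eight-week value, and with it any check of the missing-data assumption.
- *The comparison is of treatment completers.* This does not hold either. Treatment ends by week 10 whatever the attendance, so someone who attends few sessions but does not drop out is still assessed. Someone who finishes the programme is unaffected at six months.
- *The sentence may only mean that no extra measures are taken for drop-outs.* It follows directly on the sentence about additional analyses, and follow-up is timed from randomisation. This reading is possible but less natural. If it is what the authors meant, the sentence still needs rewording.
- *Sensitivity analyses may sit in an analysis plan that is not shown.* This stands. The sentence on additional analyses follows the clause on interim analyses and need not exclude missing-data checks, so their absence is not part of the point.
- *The bias is small against sampling error.* With SD 2.5 and 31 per group, the standard error is 2.5 × √(2/31) = 0.635, so even 0.6 points is within one standard error. This is true, but the confidence interval makes no allowance for a systematic shift.
- *Nothing in the article shows that drop-out will differ between arms.* This is correct, and it is why the size is given as a range under assumptions.

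**Conclusion.** The concern holds in this limited form. The rule conflicts with the stated intention to treat. The primary comparison will use eight-week data from patients who had not dropped out, plus missing at random given arm and baseline. It estimates what would have happened had drop-outs resembled stayers, not the effect in everyone randomised.

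The bias cannot be computed from the documents. Under the assumptions above it is about 0.1 to 0.6 pain points, or 5% to 30% of the 2-point target. It is about zero for the contrast if drop-out rates and outcome gaps are equal in both arms, though each arm's mean improvement would still be overstated if drop-outs do worse. The conflict in the text does not depend on these figures.

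**What to change.** Replace the sentence on drop-outs with:

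> Participants who stop treatment remain in the trial; the 8-week and 6-month outcomes will be sought from every randomised participant regardless of sessions attended, unless consent to follow-up is withdrawn.

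If a participant cannot attend in person, the existing blinded assessor may obtain the pain rating and the Roland Morris questionnaire by telephone. The pain rating is already given verbally and the questionnaire has yes/no items.

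The cost is some extra contacts and a different mode of collection for a few patients, since the Assessment section plans in-person visits in the same place. Telephone contact also yields no strength, balance or algometry data. No larger sample is needed: with all 37 per group followed, t-test power is 92.4% for pain and 90.4% for disability. Treatment does not change.

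Optionally, reword the sentence on additional analyses to allow one sensitivity analysis of the missing-at-random assumption, with the method left to the statistician. The pain scores taken before each session are of limited help for this. They cover the last 24 hours rather than seven days, and exist only for sessions attended.

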## Discussion

Pilates method and aerobic exercises have been shown to improve balance and reduce pain and disability in patients with chronic low back pain [9, 16, 19]. However, studies investigating the effects of Pilates on this population generally exclude older adults or consider patients aged 18 to 80 years, which is a wide range of age, making the results not specific for older adults [21]. Moreover, older adults show a lower response rate to aerobic interventions higher than the observed in younger patients [11]. Thus, the effects of the Pilates method and aerobic exercises on older adults with chronic low back pain are poorly understood. Therefore, the results of this study will help to determine if these exercises are also effective for older adults. We believe that, with the reduction in pain, there will be an improvement in balance [52] and function with both therapies. On the other hand, Pilates may be more effective for pain and disability because exercises are more targeted to the muscles of the pelvis and trunk [12, 44]. If our hypothesis is proven, this may increase the treatment options that clinicians can offer to patients, considering their preferences.

Therefore, the results of the present study will contribute to more accurate estimates of the therapeutic effects of Pilates and aerobic exercises in older adults and will be the largest randomized controlled trial in this field. The present study will be conducted with low risk of bias to obtain an eight score on the PEDro scale. Therefore, a sample calculation has been performed to identify a significant clinical effect and a pragmatic study has been proposed, taking into account the individuality of each patient through an exercise protocol (Additional file 1: Appendix 1 and Additional file 2: Appendix 2) and providing individualized therapies tailored to each patient. We believe that the results of this study may help physical therapists to make clinical decisions based on a high-quality methodological study. The results should be published in an international scientific journal after data collection.

